### Participants

#### Inclusion criteria

Meet the diagnostic criteria for KOA set by the ACR in 2019 [25]Age between 40 and 60 years oldKellgren-Lawrence (KL) grade II to III based on radiographic classification [26]Have a minimum score of 25 on the Western Ontario and McMaster Universities Osteoarthritis Index (WOMAC) total scoreSign an informed consent form

#### Exclusion criteria

Knee or hip arthroplastyAny uncontrolled non-musculoskeletal conditions that would make testing difficult and uncomfortable, such as unstable heart conditionsNeurological condition that affects lower-limb strength or walk (e.g., stroke)Have a contraindication for TMS use such as: the existence of metal in the skull or implanted devices, epilepsy history, pregnancyUse of drugs that might affect cortical electrical activity (anticonvulsants, antidepressants or antipsychotics)Have a contraindication for MRI use, such as: pacemaker, metal implant etc.

#### Drop-out criteria

Inability to return for treatment for any reasonAdverse events occur due to treatmentParticipants who receive other interventions to treat KOA or others that may interfere with the results of this study (e.g., using intra-articular or oral corticosteroids; post-surgical knee, knee or hip joint replacement surgery, tibial osteotomy; participating in regular physical exercise, such as swimming, cycling, etc.)

### Recruitment, enrollment and randomization procedures

All patients with KOA will be recruited from the orthopedics or joint surgery department of Shanghai Seventh People’s Hospital in China and communities around the hospital. Recruitment methods will include posters, online advertisements, and leaflets. We will communicate with prospective participants about the study details. After the patients voluntarily sign the informed consent, they will be invited to participate in the study. Recruitment will start from 1 October 2023, until when 148 participants are enrolled.

A total of 148 eligible participants will be assigned to four groups at a 1:1:1:1 ratio using stratified randomization with gender, age and KL grade as factors in this research. The stratified randomization will be achieved as follows: Firstly, participants will be invaded into men and women two groups. Secondly, the two groups will be grouped by age (< 50 and ≥ 50). Lastly, the four groups will be grouped by KL grade (II and III), a total of 8 subgroups. In these eight subgroups, the subjects will be randomly regrouped the QT group, HT group, ST + Q group and HT + Q group. Finally, all four groups will be regrouped into four new groups to minimize the bias of the final results. The randomization procedure is performed by an independent research assistant who is not comes into contact with the participant at any point prior to randomization and is not involved in the data collection using Microsoft Excel to generate the random number (https://www.microsoft.com).

### Allocation concealment and blinding

Allocation concealment will be performed by using sealed, opaque envelopes which will hide a serial number. Additionally, an independent study researcher will open the envelopes in sequence after participants complete all baseline assessments to avoid selective bias. Due to the visibility of the quadriceps strength training intervention, physiotherapists and patients cannot be blind to intervention allocation. Therefore, the blinding will only be applied to the assessors and statisticians who responsible for data collection and final statistical analyses in this study to avoid implementation bias and measurement bias. Importantly, they will not participate in the participant recruitment process.

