## Methods

### Study design

This study will be a randomized controlled trial with a parallel-group design. A total of 148 eligible participants will be assigned to the quadriceps strength training (QT group); high frequency rTMS (HT group); sham rTMS and quadriceps strength training (ST + Q group); high frequency rTMS and quadriceps strength training (HT + Q group) at 1:1:1:1 ratio using stratified randomization with gender, age and Kellgren-Lawrence (KL) grade as factors. A brief flowchart of the entire study is shown in Fig. 1 and the schedule of events is provided in Table 1. The study protocol was approved by the Ethics Committee of Shanghai Seventh People’s Hospital (2022-7th-HIRB-065) and registered in the Chinese Clinical Trial Registry (ChiCTR2300067617).

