### Interventions

All participants will receive usual care management, including health education and physical therapy when necessary. Six qualified physiotherapists who have attained the physical therapist’s certification with over 5 years of experience will be trained beforehand to instruct and guide patients in carrying out these exercises. The interventions in four groups will be carried out 5 days per week for a total of 12 weeks.

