### ST + Q Group

In the ST + Q group, sham rTMS will be delivered with the coil angle rotated 90° and only one wing of the coil touching the scalp of the participant to avoid inducing actual stimulation. The parameters, including noise, time, and frequency of the sham rTMS, will be the same as HT groups [34]. Each patient will receive sham rTMS daily for five consecutive days.

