### HT + Q Group

In the HT + Q group, the participants will receive active High-frequency rTMS and quadriceps strength training intervention with randomization of treatment order. The parameters, including noise, time, and frequency of the High-frequency rTMS, will be the same as HT groups, and the detail of quadriceps strength training will be the same as described above.

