We recognize this study also has limitations. First, the blinding cannot be performed for the participants and the study operator, because of the visibility of the quadriceps strength training intervention, which might increase the risk of detection bias during the study’s implementation. Second, the exercise training in this protocol is only focuses on quadricep strengthening and not strengthening the whole kinetic chain. Although quadriceps weakness is closely related to the occurrence and development of KOA, strengthening the whole kinetic chain may have greater rehabilitation benefits for KOA than alone quadriceps strengthening. Third, account for the absence of direct evidence on rTMS for improve pain of KOA, we incorporated the effect size of rTMS in alleviating pian of the patients with fibromyalgia in sample size calculation [24]. While there are distinctions between the two types of disease, they both involve central sensitization.

In conclusion, the study will provide evidence to show whether there are synergistic effects following High-Frequency rTMS act on M1 combined with quadriceps strength training and clarify the mechanism of action. The study will help provide rehabilitation prescription recommendations for people with KOA.

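### Visible training is no reason to leave the training physiotherapists unblinded between ST + Q and HT + Q, the only contrast that isolates active stimulation

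*Protocol article*

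**What the plan says.** All statements are in the Protocol article.

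- **Allocation concealment and blinding:** "Due to the visibility of the quadriceps strength training intervention, physiotherapists and patients cannot be blind to intervention allocation". It follows that "the blinding will only be applied to the assessors and statisticians who responsible for data collection and final statistical analyses". The section adds that this protects against implementation bias as well as measurement bias.
- **Discussion (limitations):** the same reason is repeated, "the blinding cannot be performed for the participants and the study operator, because of the visibility of the quadriceps strength training intervention". The only risk named there is detection bias.
- **Interventions:** six physiotherapists "will be trained beforehand to instruct and guide patients in carrying out these exercises". Interventions in all four groups run 5 days per week for 12 weeks. The article does not say who operates the coil or whether that person also supervises training.
- **Study design:** one arm is "sham rTMS and quadriceps strength training (ST + Q group"); another is active high-frequency rTMS with the same training.
- **ST + Q Group:** "sham rTMS will be delivered with the coil angle rotated 90° and only one wing of the coil touching the scalp". On matching: "The parameters, including noise, time, and frequency of the sham rTMS, will be the same as HT groups".
- **HT + Q Group:** for the training component, "the detail of quadriceps strength training will be the same as described above".

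**The concern.** A visible treatment prevents blinding only between arms that differ in that treatment. ST + Q and HT + Q do not differ in it. The reason given therefore does not support the conclusion for this pair, and nothing in the article keeps coil status from the staff who supervise training.

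HT + Q versus ST + Q is the contrast the sham arm exists for. HT + Q versus QT mixes active stimulation with coil contact, noise and attention. Contrasts with HT mix in the presence or absence of training. If supervisors who know coil status encourage active-coil participants more, the extra effort could change self-reported pain (VAS) or peak torque. Blinded assessors would then record that difference accurately, and it would be read as an rTMS effect. With coil status and coaching tied together, the analysis could not separate them.

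The claim that blinding assessors and statisticians avoids implementation bias hides the gap. Neither group delivers treatment, so blinding them cannot prevent unequal delivery.

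**Working it through.** **1. Does visible training reveal the arm?**

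| Comparison | Training differs? | Coil differs? | Does seeing the training tell the arms apart? |
|---|---|---|---|
| HT vs any training arm | yes | varies | yes |
| QT vs ST + Q or HT + Q | no | coil absent vs present | no, but the presence of coil sessions does |
| ST + Q vs HT + Q | no | sham vs active | no |

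Only in the last row are both components present in both arms. There, the 90° rotation is visible to whoever places the coil, so that person cannot be blinded. Someone who only supervises training need not see it.

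**2. Could anything else in the text reveal the arm to a trainer?** Yes, as written, in two places.

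- *Order.* The HT + Q section randomizes the order of the two treatments. No order is stated for ST + Q.
- *Coil schedule.* The ST + Q section describes sham sessions as daily over five days in a row. The Interventions section gives 5 days per week for 12 weeks for all groups.

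These sections must be reconciled with each other, or a trainer could infer the arm from order or attendance.

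**3. Exposure.** 5 sessions per week × 12 weeks = up to 60 supervised sessions per participant.

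**4. Sample size.** The planned total is not affected. The stated 116 reproduces with the between-groups noncentral F, λ = f²·N·m / (1 + (m − 1)ρ), f = 0.24, m = 6 and 4 groups, if ρ = 0.5 is assumed (the article gives no ρ): λ = 0.0576 × 116 × 6 / 3.5 = 11.45, power 0.806. Then 29 / (1 − 0.20) = 36.25, rounded up to 37 per arm, 148 in total.

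**5. Illustration of what a coaching difference could do.** Every bias size and SD here is an assumption; the article gives neither. Suppose active stimulation does nothing and unequal encouragement shifts week-12 VAS by d. With n = 37 per arm, a two-sample t-test has 72 degrees of freedom and noncentrality d / (SD·√(2/37)). At SD 2.0 cm the standard error is 2.0 × 0.2325 = 0.465 cm; at SD 2.5 cm it is 0.581 cm.

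| Assumed shift d | Share of the 1.16 cm MCID | SD 2.0, α = 0.05 | SD 2.5, α = 0.05 | SD 2.0, α = 0.05/6 | SD 2.5, α = 0.05/6 |
|---|---|---|---|---|---|
| 0.2 cm | 17% | 7.1% | 6.3% | 1.4% | 1.2% |
| 0.3 cm | 26% | 9.8% | 8.0% | 2.3% | 1.7% |
| 0.5 cm | 43% | 18.6% | 13.6% | 5.6% | 3.6% |

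The last two columns apply Bonferroni over all six pairs of arms (nominal level 0.83%), since the Statistical analysis section allows that correction for post hoc comparisons if necessary. The planned repeated-measures analysis is not modelled. The table shows only how a bias of a given size would carry through; it does not estimate that bias.

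**The case against.** **The stated aim is the combination against training alone.** Trainers cannot be blinded for HT + Q versus QT, because one arm attends coil sessions and the other does not. This stands, and the point does not touch that comparison. But the article calls the trial sham-controlled, and the sham arm has no other use than the contrast with HT + Q.

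**Trainers cannot vary the load.** A reader might infer from the QT Group section, where the program is to be modified, that trainers could load active-coil participants more heavily. The text does not support this. The modification follows the device manual, is meant to reduce risk, and is not given to individual therapists. Velocities, repetitions, sets and rests are fixed. What remains is unequal encouragement and effort.

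**Blinding trainers alone would fail.** This stands. The article unblinds patients in the same sentence and for the same reason. A patient who knows the coil status can tell the trainer, and can also bias the self-reported VAS directly. The order and schedule differences could reveal the arm as well. The remedy must cover all of these.

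**Roles may already be separate.** Possible, since the article does not name the coil operator and a staff rota can be left to a fuller document. But the article does not merely omit the safeguard: it states that physiotherapists cannot be blinded and limits blinding to assessors and statisticians.

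**The limitation is already disclosed.** Only in part. The Discussion repeats the same faulty reason and names detection bias, not unequal delivery of treatment.

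**The size is unsupported.** This stands, and the rates shrink considerably under Bonferroni.

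**Conclusion.** The point holds as a flaw of reasoning in the blinding section that leaves an avoidable gap in the design. Visible training does not justify leaving training supervisors aware of coil status in ST + Q versus HT + Q, and blinding assessors and statisticians does not prevent implementation bias.

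The consequence is a risk of performance bias in that one contrast, through encouragement over up to 60 sessions. Its size cannot be derived from the document. A reader might take 7%–19% (SD 2.0 cm) or 6%–14% (SD 2.5 cm) as the trial's true false-positive rate. That is not supported: those figures rest on assumed shifts of 0.2–0.5 cm, assumed SDs and an unadjusted week-12 t-test, and become 1.4%–5.6% and 1.2%–3.6% with Bonferroni over six pairs. Nor does the document show that unequal coaching will occur, that training load would differ, or that the coil operator is also the trainer.

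The change is worth making because the article describes the trial as still in preparation, and the gap cannot be repaired by analysis afterwards.

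**What to change.** 1. In ST + Q and HT + Q, separate coil operation from training supervision. The coil operator knows active or sham status and takes no part in training. The training physiotherapist is told only that the participant is in a coil-plus-training arm, and does not attend coil sessions.
2. Keep coil status off the training record.
3. Withhold active or sham status from participants in these two arms. Without this, step 1 can be undone by a remark during training.
4. Reconcile the Interventions, ST + Q Group and HT + Q Group sections on treatment order and coil schedule, so that neither reveals the arm. Which order or schedule to use is for the investigators.
5. Reword the blinding section and the matching limitation so that blinding of therapists and patients is called impossible only for comparisons that involve QT or HT. Delete the claim that blinding assessors and statisticians avoids implementation bias.

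**Cost:** a staff rota, an adjusted training record and a few sentences. Sample size, outcomes and analysis are unchanged. Scheduling the two sessions becomes somewhat less flexible. The intention is to do this within existing staff. The six physiotherapists are described as trained for the exercises and the coil operator is not identified, so that no extra staffing is needed is an assumption the investigators should confirm.

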### Interventions

All participants will receive usual care management, including health education and physical therapy when necessary. Six qualified physiotherapists who have attained the physical therapist’s certification with over 5 years of experience will be trained beforehand to instruct and guide patients in carrying out these exercises. The interventions in four groups will be carried out 5 days per week for a total of 12 weeks.

### QT Group

In the QT group, the participants will receive 20 min quadriceps strength training intervention by using Biodex Multi-Joint System 3 dynamometer (Biodex Medicalt, Shirley, NY, USA). The 12- week intervention duration period has been chosen based on evidence that at least 12 sessions of supervised exercise are required for exercise to be effective in KOA, with a number of studies demonstrating symptom improvement in KOA after 8–12 weeks of exercise [27]. Thus, 12 weeks should be sufficient to show improvement in this population. We will modify the program according to the user’s manual to reduce the risk to participants and check the device for calibration errors. All participants will be informed how the test will be and its purposes. They will conduct two familiarization sessions before the formal intervention to ensure that they feel comfortable during the exercises and perform the technique correctly. After familiarization sessions, participants will be instructed to sit in an isokinetic dynamometer and the V elcro® fixation straps will be tied around the chest, hip and distal thigh of the training limb to prevent compensatory motion from occurring. The dynamometer axis will be aligned with the canter of the lateral femoral condyle. The lever arm will be adjusted according to the training leg length and the resistance will be applied anterior to the ankle joint. The training knee will be kept at a 90° flexed position and they will be instructed to extend knee at angular velocities of 60°/sec, 90°/sec and 120°/sec with 15 repetitions in 3 sets. Rest periods of 30 s between each test extension and 2 min between each velocity will be given. Training will be performed 5 days per week for 12 weeks. A regular physiotherapist will conduct all isokinetic testing with verbal stimuli. Outcome parameters will be assessed by an independent evaluator, who is experienced in handling isokinetic devices [28]. The peak torque (TQPEAK), TQPEAK adjusted for body weight (TQPEAK/BW) and agonist–antagonist (agon/antag) ratio will be the outcomes.

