### Outcomes

Participants will be assessed by other physiotherapists blinded to the group allocation at different time points based on different assessments shown in Table 1. Additionally, baseline age, gender, symptoms, disease severity, duration, previous treatment and medication will be recorded using a questionnaire (in week 0). The primary end-point is the 12 weeks and all side effects during the study also will be recorded in real time.

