#### Secondary outcomes: Muscle strength

The maximal isokinetic muscle strength will be assessed by the Biodex Multi-Joint System 3 dynamometer (Biodex Medicalt, Shirley, NY, USA). Isokinetic exercise is a mode of speed-constant training, that can be used at low, moderate and high velocity for different evaluations and rehabilitation programs and provides reliable data. It is actually always used to quantify muscle strength, treatment and rehabilitation efficacy with mechanical or neurological instability of the knee or ligament injury [37].

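### The protocol conflicts on who conducts and verbally encourages the isokinetic strength test, so assessor blinding is not secured for the strength outcomes

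*Protocol article*

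**What the plan says.** All references are to the protocol article. The Abstract describes the trial as assessor-blind. Five later statements bear on the strength test.

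- Allocation concealment and blinding: "physiotherapists and patients cannot be blind to intervention allocation". The reason given is that the training is visible. The section then says that "the blinding will only be applied to the assessors and statisticians who responsible for data collection and final statistical analyses in this study".
- Interventions: six physiotherapists "will be trained beforehand to instruct and guide patients in carrying out these exercises". These are the treating staff.
- QT Group: "A regular physiotherapist will conduct all isokinetic testing with verbal stimuli". The next sentence reads: "Outcome parameters will be assessed by an independent evaluator, who is experienced in handling isokinetic devices". The paragraph closes by naming the measures: "The peak torque (TQPEAK), TQPEAK adjusted for body weight (TQPEAK/BW) and agonist–antagonist (agon/antag) ratio will be the outcomes".
- Outcomes: "Participants will be assessed by other physiotherapists blinded to the group allocation at different time points".
- Secondary outcomes: Muscle strength: "The maximal isokinetic muscle strength will be assessed by the Biodex Multi-Joint System 3 dynamometer". This section names no tester.

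The status of the strength measures also varies. The outcome section lists muscle strength as secondary, whereas the Statistical analysis and Discussion sections name peak torque among the primary outcomes.

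**The concern.** Isokinetic peak torque is a maximal-effort measurement. The machine records it objectively, but what it records depends on how hard the participant pushes, and verbal encouragement is meant to raise that effort. Blinding therefore matters most for the person who conducts the test and gives the encouragement. A second person who assesses the parameters cannot undo an influence on effort that has already been made.

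The VAS, KOOS and SF-36 are self-reported by participants whom the protocol describes as unblinded. Strength is the clinical effectiveness outcome for which a blinded assessor can add most protection. If the conductor knows the arm, encouragement could differ between arms, and a difference in torque could not be attributed with confidence to the treatment.

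**Working it through.** The point concerns who does what, so the check sets the statements side by side.

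1. **Who conducts the test and encourages the participant?** QT Group: a regular physiotherapist. That person's blinding status is not stated.
2. **Who assesses the isokinetic parameters?** QT Group: an independent evaluator with experience of the device. Independence is stated; blinding is not.
3. **Who assesses outcomes in general?** Outcomes: other physiotherapists, blinded. Data Availability gives a further description, under which blinded and independent research assistants collect the data.
4. **Are physiotherapists blinded?** Allocation concealment and blinding: no, without exception. Outcomes: some are.

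Now take each reading of *regular physiotherapist*.

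- If this is one of the six treating physiotherapists, the conductor is unblinded, and the strength test departs from the rule under Outcomes.
- If this is one of the blinded assessors, the test is protected. But the unqualified statement that physiotherapists cannot be blinded is then wrong for this person, and nothing in the text says that the person is blinded.
- If the word only means the usual person, or the same person each time, blinding is left open.

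Only the second reading supports the assessor-blind claim, and the text does not select it.

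**When the exposure arises.** Under Allocation concealment and blinding, envelopes are opened after all baseline assessments. The baseline test therefore precedes allocation, and only the later tests are exposed. Comparing change from baseline would not cancel an influence that acts only on those later tests.

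**Illustration of size.** The plan gives no figure for this, so the shift is an assumption. The 37 per arm comes from Sample size calculation: 116/(1 − 0.20) = 145, rounded up to 4 × 37 = 148. For a two-sided 5% comparison of two arms with no true difference, and a shift of b SD in measured torque:

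- shift in the test statistic = b/√(2/37) = b/0.2325
- false-positive rate = P(|Z + shift| > 1.96)

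| Assumed b (SD) | Shift | False-positive rate |
|---|---|---|
| 0 | 0 | 0.050 |
| 0.1 | 0.430 | 0.071 |
| 0.2 | 0.860 | 0.138 |
| 0.3 | 1.290 | 0.252 |

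This is a simple two-arm test, not the planned four-group repeated-measures analysis with Bonferroni post hoc comparisons. It shows only that even a modest shift, if present, would matter at this sample size.

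**The case against.** A reader might infer that peak torque is shown not to be assessor-blind, that the bias would favour the combined arm, and that the false-positive rate would be 7% to 25%. The documents do not support this, for the following reasons.

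- The reason given for not blinding physiotherapists is the visibility of the training, which points to treating staff. The Outcomes section shows that other physiotherapists are blinded. The tester's status cannot be deduced from the job title.
- The text does not say that the independent evaluator acts only after the test. Experience in handling the device also fits someone who operates it at assessment, and on that reading QT Group and Outcomes could agree.
- The sentence sits in a paragraph on training that mixes training and test wording, so it may partly describe supervised training.
- Muscle strength is listed as secondary in its own outcome section, and the VAS is untouched.
- Between the two arms that combine training with real or sham stimulation, both train. Seeing the training does not by itself tell a tester which stimulation was real.
- The direction is conjecture, and the shifts in the table are invented for illustration.

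All of this stands against the stronger reading. It does not remove the conflict. The sentence speaks of testing, comes after a separate sentence on the training schedule, and is followed by the outcome measures. It is also the only text that says who conducts the test. The limitations paragraph of the Discussion itself says that the study operator cannot be blinded and that this may increase detection bias. Nor is this detail that an article may leave to a fuller document: the article makes a definite statement that does not fit its own blinding rule.

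**Conclusion.** The concern holds as an unreconciled description, with moderate confidence. The sections on blinding, on the QT Group and on outcomes conflict about who conducts and encourages the isokinetic test and whether that person is blinded. For peak torque, peak torque per body weight and the agonist–antagonist ratio, the assessor-blind claim is therefore not secured. This rests on two premises: that the QT Group sentence governs outcome tests at least in part, and that measured torque responds to encouragement. The direction and size of any bias are unknown. It should be corrected, the more so because two sections treat peak torque as primary.

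**What to change.** Replace the sentence on testing in the QT Group section, and preferably move it to the muscle strength outcome section, with wording such as:

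> All isokinetic outcome tests, in every arm and at every visit, are conducted and encouraged by the blinded assessors described under Outcomes, who deliver no trial treatment, using one scripted set of verbal commands. The evaluator of the isokinetic parameters is also blinded to allocation. The regular physiotherapist takes part in training sessions only.

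In the section on blinding, limit the statement that physiotherapists cannot be blinded to those who deliver treatment, and align the description of data collectors under Data Availability.

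The change costs protocol wording and a short command script. The protocol already provides blinded physiotherapist assessors and an evaluator who knows the device, so the main downside is scheduling test visits around them. The number of blinded assessors is not given, so whether they can cover every visit needs checking. The version at hand describes the trial as still in preparation, so under that version the change could be made before any test is run.
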